## Methods/design

### Study design

This study is a double-blind, randomized, controlled, multicenter trial. After giving written informed consent, eligible participants will be randomly assigned to placebo or intervention for 3 months. Outcome parameters will be measured at baseline, at 6 weeks, and at 3 months. In Fig. 1, we show the flow chart of this study. The SPIRIT (Standard Protocol Items: Recommendations for Interventional Trials) checklist for study protocols is provided as an Additional file 1.

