### Randomization and blinding

Patients will be randomly assigned to either intervention or control group at an allocation ratio of 1:1. All investigators, medical staff, statisticians, and participants are blinded to the intervention. The statistician generates the allocation sequence and delivers it to the nutritional company responsible for the preparation of the product and placebo. The nutritional company produces the research product and placebo using the same packages without labels of the company or product name. We do not mention the product or company’s name to the participants. The sachets are packaged in boxes containing the appropriate amount for a 3-month intervention of an individual subject. The boxes are labeled with a unique numerical code, derived from the generated allocation sequence. They will be given to the participants in consecutive order. To avoid bias, the consecutive order of the labeled boxes is strictly followed. Thus, the first recruited patient is handed box number 1, the second patient is handed box number 2, and so on, regardless of the center of recruitment. Furthermore, the nutritional company prepares two identical sealed boxes, each containing 114 numerical coded envelopes with the respective treatment allocation inside. One sealed box will be stored at a secured place where only the principal investigator has direct access; the other sealed box will be kept at a secured place at the office of the head of the department. Only in case of a medical urgency is the blinding code to be broken. The designated physician and the principal investigator are ultimately responsible for the final decision of breaking the code for a single subject. Otherwise, decoding will first take place after a blind review including preliminary statistical analyses of the primary outcome data by an independent statistician. In all cases, unblinding will take place in the presence of a witness.

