### Sample size calculation

Considering a clinically relevant effect of 20% change of albumin excretion rate (AER), which is half the effect of angiotensin-converting enzyme inhibitors (ACEis) on AER [24, 25], we estimated that the average AER of 100 decreased to 80 μg/min albumin (standard deviation 40) in the intervention group compared with no expected change in the placebo group. With a two-sided alpha set at 0.05 and power at 0.80 and a correlation of 0.70 between the three repeated measures, we calculated that at least 48 patients in each study group (i.e. 96 in total) would be required [26].

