##### Study procedure

At baseline, 6 weeks, and 3 months, 24-h urine will be collected for AER measurements. Information about demographic variables, lifestyle, adverse effects, compliance, and food intake will be collected by using standard questionnaires. The urine collection procedure starts in the morning and lasts 24 h; it stops at the same time point it started the day before. During collection, all of the produced urine is collected in a container that was handed out to the patient at the outpatient clinic. Within a couple of hours after the collection, urine is delivered in the outpatient clinic. AER is measured the same day as soon as possible after delivery. The patient is instructed to keep the container with urine in a dark and cool place at room temperature until delivery. At baseline and after 3 months, blood samples will be collected for determination of ADMA, sVCAM-1, sICAM-1, IL-6, and vWF and for measuring HbA_1c_ fasting glucose, lipids, creatinine, and estimated glomerular filtration rate (eGFR). Non-fasted venous blood is collected in EDTA tubes at a random moment of the day at the outpatient clinic. Plasma samples will be stored at −80 °C until analysis. Although patients are not required to fast before blood collection, we do keep a record of whether they fasted or not. In addition, body weight, blood pressure, and waist/hip circumference will be measured. In Fig. 2, we show a schedule of the study procedures. All participants receive usual care as provided by their diabetes team and must continue all of their prescribed medication, including adjustments when required. Since this may potentially affect our outcome measures, all used medications, dosage modifications, and other medical interventions during the trial will be recorded to adjust for this potentially confounding effect. We will ask the participants to keep their current lifestyle unchanged. There are no dietary restrictions during the study, except for the use of specific dietary supplement products containing at least 25 mg MOF. To control for dietary flavanols in regular food, we will use detailed dietary questionnaires to calculate the amounts.

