##### Statistical analysis

All analyses will be conducted in accordance with the intention-to-treat principle. We will use the mean (in case of normal distribution) and median values (in case of non-normal distribution) as measures of central tendency for numerical data and the standard deviation and interquartile range as measures of variability, respectively. Mixed modeling will be applied for longitudinal analyses of the data. Mixed modeling can efficiently handle data with missing and unbalanced time points. Three levels in the models will be postulated. The participating centers constitute the upper level, the patients the middle level, and their repeated measures the lower level. First, for each outcome variable, a model will be postulated, and the primary or secondary outcomes will be dependent variables. The models will include treatment group, time, and logarithm of time and treatment-time interactions as fixed effects. The deviance statistic [29] using restricted maximum likelihood [30] will be applied to determine whether the covariance structure should also include slope and intercept-slope interaction next to the intercept. No interim analysis will be performed. Analyses will be carried out by using SPSS version 21.0 (IBM, Armonk, NY, USA) (http://www-01.ibm.com/support/docview.wss?uid=swg21608060).

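### The random-slope deviance test cannot be run for the five two-visit plasma markers, and for AER it can add about one point of type I error if correlation decays mildly

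*Protocol article*

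**What the plan says.** The Statistical analysis section sets up one mixed model per outcome, with centres, patients and repeated measures as its three levels. Fixed effects are group, time, log time and the interactions of treatment with time. The within-patient structure is not fixed in advance: the REML deviance statistic "will be applied to determine whether the covariance structure should also include slope and intercept-slope interaction next to the intercept". The section gives neither a level for this test nor a fallback, and it does not limit the step to particular outcomes.

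The visit schedule differs by outcome. Under Study procedure, "At baseline, 6 weeks, and 3 months, 24-h urine will be collected for AER measurements", but "At baseline and after 3 months, blood samples will be collected for determination of ADMA, sVCAM-1, sICAM-1, IL-6, and vWF". The Study design section makes no such distinction: "Outcome parameters will be measured at baseline, at 6 weeks, and at 3 months".

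The Sample size calculation assumes equal correlation at every lag: "With a two-sided alpha set at 0.05 and power at 0.80 and a correlation of 0.70 between the three repeated measures". Primary outcome measure defines the endpoint as the group difference in the course of AER between baseline and 3 months.

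**The concern.** Two separate things look wrong.

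- **Markers.** A slope variance and an intercept-slope covariance cannot be added to an intercept variance and a residual when each patient contributes two values. The rule covers all five marker endpoints, yet the article's own blood-sampling schedule does not allow it.
- **AER.** A random intercept forces equal correlation at all lags. If the baseline-to-3-month correlation is lower than the adjacent ones, that model understates the variance of the longest-interval change, which is the primary contrast. The deviance test should catch this, but with 96 patients it will often miss a mild departure. The analysis then continues with the wrong standard error. At stake are p-values and intervals for the primary result that are slightly too optimistic.

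**Working it through.** **The plan's own figure.** From Sample size calculation: difference 20, SD 40, two-sided alpha 0.05, power 0.80, correlation 0.70. The basic formula gives n per group = 2(1.960 + 0.842)² × 40²/20² × f = 62.8 × f.

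- Single follow-up value, f = 1: 63.
- Mean of three measures, f = (1 + 2 × 0.7)/3 = 0.8: 50.2, so 51 (power at 48 is 0.782).
- Change score, f = 2(1 − 0.7) = 0.6: 37.7, so 38 (power at 48 is 0.885).

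None gives exactly 48. Allowing 20% dropout on the change score would (38/0.80 = 47.5), but no dropout rate is stated. Nothing below depends on how 48 was reached, so I take 48 per arm as given.

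**Two-visit markers.** Let a be the intercept variance, c the slope variance, b their covariance and s the residual variance, with visits at 0 and T:

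- Var(baseline) = a + s
- Cov(baseline, 3 months) = a + bT
- Var(3 months) = a + 2bT + cT² + s

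That is three equations in four unknowns. For any δ, replacing (a, s, b, c) by (a + δ, s − δ, b − δ/T, c + 2δ/T²) leaves all three moments unchanged, so the slope model is not identifiable. With three visits there are six moments, and the rank is 4 for 4 parameters, so the model can be fitted. The fixed part has the same problem: two time points support one time effect, so time and log time cannot be separated.

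The random intercept alone remains usable. With complete two-visit data it gives the change-score test. Its simulated size was 4.9% to 5.0%, including a case with unequal variances at the two visits.

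**AER: why the random intercept fails under decay.** Take equal variances, adjacent correlation r1 and outer (baseline to 3 months) correlation r2. The random intercept estimates the change variance from the average correlation r̄ = (2r1 + r2)/3. Its variance is therefore a fraction k = (1 − r̄)/(1 − r2) of the true one, and the size of a nominal 5% test is about 2[1 − Φ(1.96√k)].

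Example at 0.70/0.60: r̄ = 0.667 and k = 0.333/0.400 = 0.833. With SD 40 and 48 per arm, the true standard error is 40 × √0.80 × √(2/48) = 7.30, and the random intercept reports 40 × √0.667 × √(2/48) = 6.67. The size is 2[1 − Φ(1.79)] = 7.4%.

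**AER: after the pre-test.** Simulation under no effect used 48 per arm, three visits, complete normal data, group-by-visit means and REML. The slope was kept if the deviance exceeded 5.99 (chi-square, 2 df, p < 0.05). The contrast was 3 months minus baseline. Where a range is shown, it spans two separate simulations.

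| r1 / r2 | k | Random intercept alone (formula) | Slope selected | Size after pre-test |
|---|---|---|---|---|
| 0.70 / 0.70 (protocol) | 1.000 | 5.0% | – | 5.0% |
| 0.70 / 0.65 | 0.905 | 6.2% | 14% | 5.9% |
| 0.70 / 0.60 | 0.833 | 7.4% | 40% | 5.9–6.1% |
| 0.75 / 0.65 | 0.810 | 7.8% | 53% | 6.0–6.1% |
| 0.75 / 0.60 | 0.750 | 9.0% | 86% | 5.4% |
| 0.70 / 0.49 | 0.725 | 9.5% | 94% | 5.2% |

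Unstructured covariance gave 4.95% to 5.1% throughout. Over a wider grid the maximum after the pre-test was about 6.2%. With the boundary-mixture cut-off of 5.14, the mild cases give 5.8% to 5.9%. A 2-df joint treatment-by-time test after the same selection gives 5.1% to 5.3%.

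**The case against.** Comparing nested random-effects structures by REML deviance is a recognised practice, and the article cites method references for it. Under the only correlation the protocol states, the planned procedure holds 5.0%. The excess needs decay patterns that I supply and is confined to a middle band, since strong decay is usually detected. It also needs a 1-df reading of the primary test and an assumed level for the deviance test. A condensed article may leave both to a fuller document. The simulations omit the centre level. For the markers, the random intercept is the base model, so the natural fallback is valid.

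Most of this stands, and it limits the point to a small one. The centre omission matters little: a centre intercept is common to a patient's visits and cancels in the change from baseline. What does not fall away is the rule for the markers, since the article states a step that its own sampling schedule makes impossible. The 1-df reading is reasonable because the endpoint is worded as baseline to 3 months.

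A reader might infer more: that the primary analysis is inflated under the sponsor's own assumptions, or that marker p-values would be invalid. The documents support neither. The first needs correlation decay, which the article does not mention. The second is contradicted by the size of the fallback test.

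**Conclusion.** The point holds in a limited form.

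- **Markers:** the selection step cannot be carried out for five named secondary endpoints. This follows from the visit schedule and needs no assumption beyond the two blood draws given under Study procedure. The Study design statement of three visits conflicts with that schedule and must be reconciled with it. The consequence is an unworkable rule, with no shown effect on error rates for complete data.
- **AER:** selection adds about one percentage point of type I error at most, roughly 5.9% to 6.1% in the three mild-decay cases. This rests on assumed correlations, complete normal data, a 5% chi-square cut-off and the 1-df contrast. The excess is zero at constant 0.70 and about 0.2 point at 0.70/0.49, and it nearly vanishes for a 2-df test.

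This is worth correcting because the remedy is cheap and removes a data-driven choice from the primary analysis. It is not a reason to doubt the design.

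**What to change.** Drop the deviance pre-test. For AER, pre-specify an unstructured within-patient covariance over the three visits, keeping the centre level if wanted. Treat visit as categorical and name the treatment-by-visit contrast at 3 months as the primary test. For the five markers, use an unstructured 2x2 covariance (three parameters for three moments) or ANCOVA on the 3-month value adjusted for baseline, with no slope or log-time terms. Align the Study design sentence on visits with the blood draws under Study procedure.

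The cost is wording only, with the same data and software. For AER the unstructured model has six covariance parameters against four for the slope model, so two more. If the constant 0.70 is true, simulated power at a 20 μg/min difference and SD 40 is 0.876 with the unstructured covariance against 0.877 as planned, a loss of about 0.1 percentage point.

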## Discussion

The presence of microalbuminuria is associated with endothelial dysfunction and poor cardiovascular outcome in T2D [31]. Although microalbuminuria is associated with a number of other risk factors, it is considered an independent risk factor for CVD and cardiovascular events in diabetes [31]. The exact mechanism leading from microalbuminuria to end organ damage is not yet completely understood. Endothelial dysfunction, however, might play a crucial role in this process [32]. Hypothetically, microalbuminuria is a signal of endothelial dysfunction leading to increased permeability of atherogenic lipoprotein particles [31]. In addition to endothelial dysfunction, a number of metabolic disorders are associated with microalbuminuria leading to cardiovascular damage: transvascular leaking of albumin in vessels, elevated glomerular filtration rate, elevated blood pressure, hyperinsulinemia, elevated plasma fibrinogen levels, and altered blood lipid levels and function may also play important roles [31, 32].

Treating microalbuminuria by improving endothelial function is most probably beneficial in patients with T2D. Although ACEis and angiotensin receptor inhibitors (angiotensin receptor blockers, or ARBs) are effective treatments to achieve this goal [31, 32], use of MOF as part of the dietary management may also be an effective auxiliary strategy. The individual responses to ACEis and ARBs show large variation. They are not equally effective in treating microalbuminuria in each individual patient [32]. Besides, a remarkable percentage of treated patients with T2D will eventually develop diabetic kidney disease during the course of the disease [33]. Therefore, if MOF are proven to fulfill the specific nutrient requirement, they may become a dietary tool to manage albumin excretion in patients with T2D and microalbuminuria in general and in the insufficient responders to ACEis and ARBs in particular.

Obviously, the safety features of MOF are very important. In contrast to ACEis and ARBs, Endoclair MOF is registered as a food supplement for special medical purposes, not requiring patient monitoring upon first application. The advantageous effects of MOF on reversing endothelial dysfunction and maintaining cardiovascular health have been widely addressed in past decades; in epidemiological studies, average dietary intake of flavanols has been linked to health status [9, 13–16, 19, 20, 32, 34]. Nevertheless, there is a lack of clinical and well-conducted studies specifically addressing the effects of MOF on renal endothelial function in T2D.

We hypothesize that the use of 200 mg MOF daily for 3 months will have a beneficial effect on renal endothelial function and will result in a decrease of AER. This may lead to new insights into the dietary management of T2D patients with renal complications. MOF could have beneficial effects on endothelial function in other parts of the body as well, as suggested by previous studies [9, 13–16, 19, 20, 32, 34]. Finally, since the participants in this trial are recruited from tertiary, secondary, and primary referral centers, our study sample well represents T2D patients with microalbuminuria in general.

## Trial status

Protocol version number 3.1, June 5, 2018.

Start recruitment: January 1, 2015.

End of recruitment (estimated): December 31, 2018.

Trial sponsor: Erasmus Medical Center, Rotterdam, The Netherlands.

## Abbreviations

ACEi: Angiotensin-converting enzyme inhibitor
ADMA: Asymmetric dimethylarginine
AER: Albumin excretion rate
ARB: Angiotensin receptor blocker
BTE: Black tea extract
CVD: Cardiovascular disease
DMC: Data monitoring committee
eGFR: Estimated glomerular filtration rate
IL-6: Interleukin-6
MOF: Monomeric and oligomeric flavanols
SAE: Serious adverse event
sICAM-1: Soluble intercellular cell adhesion molecule-1
sVCAM-1: Soluble vascular cell adhesion molecule-1
T2D: Type 2 diabetes mellitus
vWF: Von Willebrand Factor
